#### Sexual Risk-Taking

The definition of at-risk sex will be serostatus specific. For serodiscordant couples, at-risk sex will be CAI with either their main or outside partners. For seroconcordant-negative and seroconcordant-positive couples, at-risk sex will be CAI with outside sex partners. While data on PrEP use and adherence will be collected, the definition of at-risk sex focuses on condom use given the CDC recommendation for continued condom use for those adopting PrEP. The incidence of at-risk sex acts will be calculated as an incidence density, with the numerator being the number of individual at-risk sex acts and the denominator being person-years of follow-up time. Comparisons of the incidence of at-risk sex acts will be made by comparing incidence densities between the two arms. Incidence rates per couple-year of follow-up will be estimated and compared using exact methods based on the Poisson distribution by using the GEE approach. Baseline covariates include race, age, and duration of relationship. Period incidence rates—6-monthly incidence density rates—of at-risk sex will be estimated by performing a GEE Poisson regression analysis of the 6-monthly counts. This will be implemented using the PROC GENMOD procedure by SAS (SAS Institute Inc) [56] and using an exchangeable correlation structure for the repeated observations of couples. The incidence density ratio, or incidence rate ratio (IRR), is the ratio of the incidence density in one treatment group (intervention arm) to that of another group (control arm). Results by each baseline covariate will be summarized as the IRR and the 95% confidence interval. These analyses will be descriptive and include analyses stratified by race/ethnicity. Prevalence of each outcome will be calculated and prevalence of outcomes will be compared in the control and intervention groups using chi-square tests or Fisher’s exact tests, as appropriate.

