## Introduction

HIV prevalence remains high among men who have sex with men (MSM) in the United States [1]. Recent research has drawn attention to the role of male dyads in the US HIV epidemic, with primary partners identified as the source of approximately one-third [2] to two-thirds [3] of new HIV infections. Given these estimates, a significant paradigm shift in HIV prevention is needed. Efforts have traditionally focused on MSM, in particular gay-identifying men, (1) as individuals versus dyads and (2) as having been the focus of messages about HIV risks, primarily in the context of casual sex. Recent research findings have illustrated high rates of sexual risk behavior for HIV with primary and casual partners, low rates of disclosure of potentially risky episodes with casual partners to primary partners, and reduced frequency of HIV testing among male couples [4-10]. In addition, relationships may convey a misplaced sense of protection [11,12], to some degree created by the historical prevention focus on reducing numbers of sexual partners among MSM [13]. The Office of the US Global AIDS Coordinator, through dissemination of prevention guidelines for MSM in the President’s Emergency Plan for AIDS Relief-supported countries, now recommends couples HIV testing and counseling (CHTC) for male couples [14].

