A vital cornerstone to prevention and linkage to care is HIV testing [43]. This paper describes the protocol for a new randomized controlled trial (RCT) that combines the CDC-recommended prevention strategy of CHTC with home-based testing for male couples via video-based counseling and testing. By using video-based technologies (eg, VSee video chat), male couples receive counseling and support from a remote online counselor, while testing for HIV at home. This combination of HIV testing efforts is needed and timely because few interventions exist for male couples, especially those who live in rural areas and areas with few LGBTQ resources. This RCT aims to examine and compare the intervention’s effects on the relationship’s ability to manage HIV risk, formation and adherence to explicit sexual agreements, and sexual risk-taking between self-reported concordant-negative and self-reported discordant male couples. Participants complete surveys at baseline, 3 months, and 6 months. It is hypothesized that couples exposed to the intervention will learn communication skills and receive psychoeducation that allows them to work together on HIV prevention planning. As a result, it is hypothesized that couples exposed to the intervention will be more likely to report discussing and forming sexual agreements and be more likely to adhere to agreements, yet also more likely to disclose if they break their agreements.

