The theoretical basis for intervention is the Couple’s Interdependence Theory (CIT) [44], a framework that combines both interdependence theory and communal coping perspectives and captures constructs central to the intervention. The framework guides the selection of measures of behavior change within the couple’s relationships. Through interdependence, both members of the couple will rely on themselves and on each other to reach individual- and/or couple-positive and/or couple-negative healthy behaviors. These outcomes will either improve or detract from the quality of the couple’s relationship. With this in mind, communal coping assists couples in achieving positive healthy behaviors that benefit both members of the couple as they cooperatively communicate to reach their desired goals [44]. These measures relate to the intervention in two ways. First, some aspects of communication and decision making within the partnership may influence the efficacy of the intervention; couples with more constructive communication styles may benefit from CHTC than would couples with less constructive communication styles. Second, some aspects of partnerships, such as efficacy around implementing behavioral change, may benefit more from CHTC. In this way, changes in key characteristics of the partnerships may be in the causal pathway between the intervention and the adoption of greater health-enhancing behaviors (ie, reduction in CAI outside of the relationship) within the partnership. The causal pathways are conceptualized as follows: couples exposed to the intervention package will receive opportunities to talk together about HIV, sexual health, and sexual agreements within their relationship through the assistance of a trained CHTC counselor and will have the ability to self-test for HIV as a couple at home. This may in turn impact communal coping, use of coping, and transformation of motivation. This may lead to initiation and maintenance of health-enhancing behaviors, which is conceptualized as reduction in sexual risk-taking (eg, CAI) within and outside of the relationship relative to couples who self-test for HIV at home without the presence of a counselor. In the research design, predisposing factors, outcome efficacy—the shared desire for the same outcome (ie, HIV prevention strategies)—and couple efficacy are collected separately from each member of the male couple before the HIV testing intervention is delivered, and will again be collected at 3-month and 6-month follow-up assessments.

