#### Linkage to Care

The percentage of HIV-positive respondents who receive a timely (<3 months) comprehensive visit—a visit including a CD4 count, viral load count, and the date of their first care visit—will be tested for significance across the two study arms. The percentages of couples who are seroconcordant negative, seroconcordant positive, and serodiscordant, as part of the description of the analysis samples, will be recorded. To assess whether the concordancy of the couple modifies the intervention effects, formal statistical tests—likelihood ratio tests in mixed models and generalized score tests in marginal models—of the null hypothesis will be conducted. The null hypothesis is that the two-way interaction effect for the aforementioned items and scales between intervention and concordancy is zero. If the statistical test does not reject the null hypothesis, the concordancy main effect in the model will be retained, removing the two-way interaction, and conclude that there is not sufficient evidence to suggest that concordancy modifies the intervention effect.

The safety of the intervention at both the individual and couple levels will be evaluated by examining reported IPV within the relationship and relationship dissolution. At the individual level, prevalence of each individual adverse outcome or any adverse outcome will be calculated. Prevalence of outcomes will be compared across the control and intervention arms, by serostatus of the couple, and by relationship duration using chi-square tests or Fisher’s exact tests, as appropriate. At the couple level, the APIM will be used to predict how an individual and his partner’s reports of dyadic characteristics affect the individual’s experience of IPV and reported relationship dissolution.

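### At-risk sex counts different acts in discordant and concordant couples, so the stated comparison of effects between couple types needs an outcome defined the same way in both

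*Protocol article*

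**What the plan says.** The protocol article is open about the rule. In the statistical analysis section on sexual risk-taking: "The definition of at-risk sex will be serostatus specific". It continues: "For serodiscordant couples, at-risk sex will be CAI with either their main or outside partners". For the other couples: "For seroconcordant-negative and seroconcordant-positive couples, at-risk sex will be CAI with outside sex partners". The same section describes IRRs comparing the two arms and lists race, age and duration of relationship as baseline covariates. Couple serostatus is not in that list.

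The Introduction sets a comparative aim: "This RCT aims to examine and compare the intervention’s effects on the relationship’s ability to manage HIV risk", and the sentence goes on to "sexual risk-taking between self-reported concordant-negative and self-reported discordant male couples". Sexual risk-taking is listed among the primary outcomes.

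Under Linkage to Care, the protocol plans a test of whether concordancy modifies the intervention effect: "The null hypothesis is that the two-way interaction effect for the aforementioned items and scales between intervention and concordancy is zero". The outcome section on sexual risk-taking records main-partner acts and outside-partner acts as separate items, with no restriction by couple serostatus. No section names a sexual-risk outcome defined identically in both couple types.

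**The concern.** One name, at-risk sex, covers two different counts. In discordant couples it is main-partner plus outside-partner CAI; in concordant couples it is outside-partner CAI alone. A counselling session could well change behaviour with outside partners by a different proportion from behaviour with the main partner. If so, the two couple types will show different IRRs even when the intervention does exactly the same thing to each behaviour in both. A reader would then see serostatus modifying the effect, when the difference comes from which acts are counted. The reverse can also happen: a real difference could be masked.

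A single IRR pooled over couple types without serostatus in the model has a related weakness. It mixes the two definitions and leans towards whichever couple type and act type supplies more acts.

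**Working it through.** The protocol states no figure that rests on this definition, so there is none to reproduce. The check is what the definition does to the ratio of IRRs.

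**Inputs.** The two definitions come from the statistical section on sexual risk-taking. The protocol gives no act rates and no assumed effect on acts, so the following are assumptions:
- *s*, the main-partner share of control-arm at-risk acts in discordant couples: 25%, 50%, 75%, 90%.
- *R_main* and *R_out*, the IRRs for main-partner and outside-partner CAI, each taken to be **the same in both couple types**, so that there is no true effect modification on either behaviour.

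**Formulas.**
- Discordant IRR = *s* × *R_main* + (1 − *s*) × *R_out*
- Concordant IRR = *R_out*
- Ratio of IRRs = discordant IRR / concordant IRR

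**Case A: outside acts reduced 30%, main-partner acts unchanged** (*R_out* = 0.70, *R_main* = 1.00). At *s* = 25%, the discordant IRR is 0.25 × 1.00 + 0.75 × 0.70 = 0.775.

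| *s* | Discordant IRR | Concordant IRR | Ratio |
|---|---|---|---|
| 25% | 0.775 | 0.70 | 1.11 |
| 50% | 0.85 | 0.70 | 1.21 |
| 75% | 0.925 | 0.70 | 1.32 |
| 90% | 0.97 | 0.70 | 1.39 |

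**Case B: main-partner acts reduced 30%, outside acts unchanged** (*R_main* = 0.70, *R_out* = 1.00). The concordant IRR is 1.00, so the ratio equals the discordant IRR.

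| *s* | Discordant IRR | Concordant IRR | Ratio |
|---|---|---|---|
| 25% | 0.925 | 1.00 | 0.93 |
| 50% | 0.85 | 1.00 | 0.85 |
| 75% | 0.775 | 1.00 | 0.78 |
| 90% | 0.73 | 1.00 | 0.73 |

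**Case C: a smaller gap between the effects** (*R_out* = 0.70, *R_main* = 0.85). The ratios are 1.05, 1.11, 1.16 and 1.19.

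**Case D: equal effects** (both 0.70). The ratio is 1.00 at every *s*.

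**With a common component.** If outside-partner CAI is used in both couple types, both IRRs equal *R_out* and the ratio is 1.00 in all four cases.

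**Pooling.** Let *w* be the share of all control-arm at-risk acts that come from discordant couples. With equal follow-up by arm, the crude pooled IRR is *w* × discordant IRR + (1 − *w*) × concordant IRR. In case A with *s* = 50% and an assumed *w* = 50%, this is 0.5 × 0.85 + 0.5 × 0.70 = 0.775. That value describes neither couple type, and it moves with *w*.

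**The case against.** The definition is a declared choice that tracks HIV-relevant exposure. On that outcome, a smaller proportional fall in discordant couples is a true statement about exposure acts. Randomisation is stratified by couple serostatus, so the arm contrast within each couple type is sound. All of this stands, and it rules out calling the definition an error or the outcome uninterpretable.

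It is also fair that the cross-type comparison of act rates is thinly specified. The statistical section on sexual risk-taking compares arms and calls its analyses descriptive. The concordancy interaction test refers to items and scales, and may not reach act counts. The sample-size section, writing about change of agreement status, makes pooling conditional on the effects agreeing across couple types. The comparison for this outcome therefore rests mainly on the aim in the Introduction. That aim is explicit, though, and names sexual risk-taking.

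Two stronger readings are tempting. The Introduction describes "primary partners identified as the source of approximately one-third [2] to two-thirds [3] of new HIV infections", so a reader might infer that main-partner CAI in concordant-negative couples is wrongly scored as carrying no risk because neither man has tested recently. The testing gap is an entry criterion, and kits are supplied after enrolment. The Results report that 88.0% of control couples returned results and 76.6% of intervention couples completed the session. The definition also names concordant-positive couples, who cannot enter the trial. This suggests, without saying so, that couple status may be updated after testing.

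The Introduction also hypothesises "reduction in sexual risk-taking (eg, CAI) within and outside of the relationship relative to couples who self-test for HIV at home", so a reader might infer that the within-relationship part cannot be answered in half the sample. But main-partner acts are collected from all men, and the same part of the Introduction elsewhere describes the target behaviour as less CAI outside the relationship.

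**Conclusion.** The point holds, confined to comparing effects between couple types and to any IRR pooled across them. As written, a difference in the at-risk-sex IRR between discordant and concordant couples cannot be separated from the difference in the acts counted. With identical effects on each behaviour in both couple types, the ratio of IRRs could lie anywhere from about 0.73 to 1.39. That range assumes a 30% reduction in one act type, none in the other, and a main-partner share of 25% to 90%. The direction depends on which behaviour responds, and the distortion vanishes if both respond equally. The actual size is unknown because the protocol gives no act rates. Arm comparisons within each couple type are unaffected.

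**What to change.** In the statistical analysis section on sexual risk-taking:

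1. Keep the serostatus-specific outcome for arm comparisons within each couple type, and report it by stratum.
2. For the comparison of effects between couple types, and for any arm-by-concordancy test on sexual risk-taking, use outside-partner CAI acts defined identically in all couples.
3. Report main-partner CAI separately by stratum as a supporting component.
4. Include couple serostatus in any pooled model. This allows for different base rates but does not make the two counts alike, so the by-stratum results should stand beside any pooled composite IRR.

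Both act types are already asked about separately, so no new data are needed. The cost is a change of wording and one or two extra models.

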### Primary Outcomes

Initiation and maintenance of health-enhancing behaviors are conceptualized as including two sets of outcomes: sexual agreements and sexual risk-taking as well as linkage and retention to HIV care.

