### Statistical Analysis: Dyadic Characteristics

#### Overview

Dyadic characteristics will be analyzed within and between couples over time by HIV status and study arm (control vs experimental). Simple *t* tests and chi-square tests will be used to investigate systematic differences among average scales between experimental and control arms and between serodiscordant and seroconcordant-negative couples. Next, regression, generalized linear mixed models, and marginal models via generalized estimating equations (GEE) will be used to model longitudinal item and scale measures. In general, participants will be nested within couples, so the participant is regarded as the experimental unit; outcomes within couples and over time are potentially correlated. Initially, an unstructured serial correlation structure for the within-subject covariance and a single correlation parameter to describe the within-couple correlation will be assumed. If the unstructured covariance structure is too weak leading to nonconvergence issues and weak identification, more structure will be placed on the residuals and stronger models will be considered, such as an exchangeable or autoregressive correlation structure. Statistical inference will be likelihood based for the mixed models while generalized score and Wald tests will be used for statistical inference in the marginal models. In the presence of missing data, both mixed and marginal models accommodate missing data (eg, dropout), although the former under a weaker (missing at random) assumption.

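### The arm comparison of at-risk sex rates joins exact Poisson inference and GEE in one sentence; they are incompatible, and the exact method would be anti-conservative for clustered act counts

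*Protocol article*

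**What the plan says.** The relevant text is under Statistical Analysis: Dyadic Characteristics, Sexual Risk-Taking. The incidence density is defined with "the numerator being the number of individual at-risk sex acts and the denominator being person-years of follow-up time". Rates are then to be "estimated and compared using exact methods based on the Poisson distribution by using the GEE approach". Next, period rates are to be estimated by "performing a GEE Poisson regression analysis of the 6-monthly counts", "using an exchangeable correlation structure for the repeated observations of couples". On software the section says: "This will be implemented using the PROC GENMOD procedure by SAS". The effect measure is an incidence rate ratio (IRR) with a 95% confidence interval.

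The Overview of the same analysis section says that "generalized score and Wald tests will be used for statistical inference in the marginal models".

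On the standing of the outcome, the Primary Outcomes section lists "two sets of outcomes: sexual agreements and sexual risk-taking as well as linkage and retention to HIV care". The analysis section on sexual risk-taking also states: "These analyses will be descriptive and include analyses stratified by race/ethnicity".

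**The concern.** An exact Poisson comparison of two rates conditions on the total number of events and asks whether they split between the arms in proportion to follow-up time. It is valid when every act is an independent event at one common rate per arm, so that variance equals mean. Here the unit counted is the individual sex act. Some couples will report none and others many, and acts by the same couple are not independent. The variance of the arm total then exceeds its Poisson value, and the interval is too narrow.

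GEE inference does not need variance to equal the mean. It is asymptotic, and with empirical standard errors it takes the variance from the observed scatter between clusters. It is not an exact method, and the Overview assigns score and Wald tests to marginal models. The two procedures can give very different p-values on the same data, and the sentence that says how rates are compared names both. Left as it is, the text lets an analyst cite the protocol for either, and the one labelled exact would give the more impressive result.

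**Working it through.** **The article's own figures.** The only calculation it gives is the power for change of agreement status under Sample Size: 52%, 67% and 85% at 150 couples per arm, and 81%, 92% and 99% at 300. With rates centred on 25% (25% − d/2 against 25% + d/2), pooled variance and two-sided 5%, these come out as 51.6, 67.2, 85.5% and 80.9, 92.6, 99.0%. They concern a different outcome and have no bearing on this point. The article gives no mean, variance or power for act counts.

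**Inputs.** The 5% type I error rate and the 100 couples per arm within each serostatus group (200 per arm pooled) come from Sample Size. The variance-to-mean ratio of couple counts, φ, is an assumption and is shown as a range.

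**Formula.** A Poisson test takes the variance of the log rate ratio as 1/A + 1/B, where A and B are the arm totals. If couple counts have variance φ times their mean, the true variance is φ times larger and the test statistic has standard deviation √φ under the null. Hence

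type I error ≈ 2 × [1 − Φ(1.96/√φ)].

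- φ = 2: 1.96/1.414 = 1.386, giving 0.166
- φ = 10: 1.96/3.162 = 0.620, giving 0.535
- φ = 38: 1.96/6.164 = 0.318, giving 0.75

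On the log scale the interval is too narrow by a factor √φ, that is 1.4, 3.2 and 6.2. The number of couples does not enter the formula, so a larger trial would not cure this.

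**Simulation.** Gamma-Poisson counts with no arm effect, 4,000 trials per setting, at 100 and 200 couples per arm. The exact test is the conditional binomial test, two-sided by doubling. The robust test is a Wald test of the log rate ratio with variance from couple-level scatter.

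| φ | Formula | Exact Poisson, simulated | Robust variance, simulated |
|---|---|---|---|
| 1 | 5% | 4.7–4.8% | 5.3–5.5% |
| 2 | 17% | 15.6–16.3% | 5.4–6.0% |
| 3 | 26% | 24.0–24.6% | 5.0–5.9% |
| 5 | 38% | 36.8–38.9% | 5.7–6.4% |
| 11 | – | 54.9–56.4% | 5.7–6.1% |
| 21 | – | 65.3–67.8% | 5.0–7.9% |
| 41 | – | 76.0–76.3% | 5.8–6.1% |

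The highest robust figure, 7.9%, is one very skewed setting (mean 2, φ = 21) with 100 couples per arm. Every other robust figure is 6.5% or less.

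A closer match to the stated model is a two-period GEE Poisson fit with exchangeable correlation and robust errors. It rejected 5.5–7.0% at φ = 3, 11 and 41 (400 trials per setting, Monte Carlo standard error about 1.1 points). An ordinary Poisson regression that ignored clustering rejected 26–27%, 57–58% and 71–78% on the same data. The protection therefore comes from the clustered, empirical variance and not from the Poisson regression as such.

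**Is φ above 1 plausible?** Preliminary Data reports that about half of 15 pilot couples were monogamous, and for concordant-negative couples only outside-partner acts count. Suppose, as an illustration, that half of couples have zero acts and the rest are exactly Poisson with mean m. The mean is m/2 and the variance m/2 + m²/4, so φ = 1 + m/2. That gives φ = 2 at m = 2 and φ = 6 at m = 10. The values of m are assumed; the direction does not depend on them.

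**The case against.** A reader might infer that the planned test has a type I error of 15 to 75%. The document does not support that, for three reasons.

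- The sentence itself names GEE, and what follows is a GEE specification: a Poisson regression in PROC GENMOD, an exchangeable working correlation by couple, and baseline covariates. The Overview gives score and Wald tests for marginal models. A two-sample exact test has no working correlation and no covariates, so the exact wording may simply be stray. Under GEE with empirical errors the error rate is close to nominal.
- The 15 to 75% range corresponds to φ of roughly 1.8 to 38. The article gives no dispersion, so any such range is an assumption.
- The section calls its analyses descriptive, and no single act-count test is named as deciding the trial. The worked power example concerns agreement change.

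It can also be said that an article commonly leaves the type of standard error to the full protocol or analysis plan. That is right, and its absence is not the complaint.

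The objection removes the unconditional error rates. It does not remove the contradiction. The sentence that says rates are compared states an unsuitable method in so many words, while the GEE sentence that follows speaks of estimating period rates. The descriptive label comes after the results by baseline covariate, and its reach is unclear. The section does say that the arms will be compared, and Sample Size counts sexual risk-taking among the outcomes for which significant change is to be detected.

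**Conclusion.** The point stands as a wrong statement of method for an outcome in the primary set: one sentence assigns the arm comparison to two incompatible procedures. The size is conditional. If the exact test were used, nominal 5% becomes about 17% at φ = 2, 54% at φ = 10 and 75% at φ = 38. If GEE with empirical standard errors clustered on couple is used, it is about 5 to 8%. The formula rests only on φ, and the simulations also on gamma-Poisson counts. That act counts exceed Poisson variation is very likely from the way the outcome is defined; by how much cannot be said from the article.

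**What to change.** Delete the reference to exact Poisson methods from the sentence on comparing rates. State instead that the between-arm IRR, its 95% interval and its test all come from the GEE Poisson (log-linear) model, clustered on couple, with empirical (sandwich) standard errors. This keeps the model, software and working correlation already named and agrees with the Overview. A negative binomial model as a sensitivity analysis is optional.

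The cost is one sentence and possibly a wider interval than the exact Poisson method would print. Nothing in recruitment or data collection changes.
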